**Fig. 2 Fig2:**
[figure not shown]
Flowchart for titration of esmolol dose. bpm, beats per minute, HR, heart rate

**Fig. 3 Fig3:**
[figure not shown]
Flowchart for management of CPP. CPP, cerebral perfusion pressure, FICE, focused intensive care echocardiography, ICP, intracranial pressure, PiCCO, pulse index continuous cardiac output, RASS, Richmond Agitation Sedation Scale

### Concomitant Interventions

Enteral or parenteral use of selective or nonselective beta-adrenergic blockers is not permitted during the intervention phase (i.e., during esmolol infusion including weaning period). Given the short elimination half-life of esmolol, a 2-h gap from termination of infusion is considered sufficient. No other specifications on the use of concomitant interventions are made.

Standard TBI management at Southmead Hospital is based on Brain Trauma Foundation guidelines [19]. Arterial pressure transducers are zeroed at the level of the external auditory meatus. Multimodality neuromonitoring is not used.

### Baseline, Intervention, and Follow-Up Data

Baseline demographics collected will include age, gender, Glasgow Coma Score, time of injury and admission, Charlson comorbidity index, beta-blocker use at admission, intracranial and extracranial injury (abbreviated injury score and injury severity score), and the Helsinki computed tomography (CT) score. Intracranial pressure directed interventions include osmotic therapy, sedation and neuromuscular blockade, hyperventilation, therapeutic hypothermia (deliberate reduction in core temperature below 35 °C), radiological investigation of elevated intracranial pressure, cerebrospinal fluid (CSF) drainage, and craniotomy or craniectomy. The schedule of assessments is shown in full in Table S1 (Supplementary Material).

### Primary Outcome

The primary end point is a continual reassessment method-derived maximum tolerated dosage escalation schedule for esmolol that combines clinically significant reduction in heart rate (defined as ≥ 15% from baseline) with maintenance of CPP.

### Secondary Outcomes

Secondary outcomes in this study are the following:Organ functionSequential organ failure assessment (excluding neurological assessment)ClinicalMortality: ICU, acute hospital, and 6-monthsLength of stay: ICU and acute hospitalDuration of mechanical ventilationBloodstream infection in ICUExtended Glasgow Outcome Score (eGOS) at 6 monthsQuality of life (EQ-5D-5L) at 6 months

### Exploratory Outcomes

Biomarkers will include cardiac troponin T, coagulation screen, glucose, lactate, and heart rate. Blood will be stored for subsequent analysis of further endothelial and other biomarkers.

Estimates of efficacy and feasibility, other than the clinical outcomes listed above, will include the following:SafetyIncidence of bradycardia (heart rate < 50 beats per minute) with or without hemodynamic compromise requiring intervention other than reduction of esmolol dosageIncidence of second-degree or third-degree heart block with or without hemodynamic compromise requiring intervention other than reduction of esmolol dosageIncidence of clinically significant hypotension (systolic blood pressure < 100 mm Hg for patients aged 50–69 years, < 110 mm Hg for others) requiring intervention other than reduction of esmolol dosageEfficacyDose and duration of vasopressor during esmolol infusionProportion of time during esmolol infusion with CPP in target range (60–70 mm Hg)Number of interventions per calendar day for intracranial pressure control during esmolol infusion (with daily and domain therapy intensity level scores)FeasibilityRates of recruitment, consent after emergency waiver and loss to follow-upNoncompliance with study protocolAcceptability

Additional funding will be sought for studies to support exploratory outcomes including biomarker analysis of stored blood and qualitative investigation of study acceptability and protocol delivery.

### Pharmacovigilance

Patients admitted to intensive care following severe TBI are critically ill and have a high baseline risk of complications of illness and of death. Medical occurrences that meet the definition of adverse events and adverse reactions may be expected features of critical illness requiring ICU care. All adverse events and adverse reactions will be considered in the context of the individual patient’s clinical condition and the natural history of severe TBI. Those who are considered by the chief investigator (or medically qualified designate) to be consistent with the patient’s critical illness do not require recording or reporting, unless the investigator considers they may relate to participation in the trial. All serious adverse events and serious adverse reactions both expected and unexpected will be recorded. For the purpose of this study, the Reference Safety Information is the Summary of Prescribing Characteristics for Brevibloc Premixed 10 mg/mL solution for infusion (Baxter Healthcare Ltd) [21].

Secondary and exploratory outcomes include assessment of organ function and significant hemodynamic side effects of esmolol infusion as a means of capturing additional safety information in the patient population. Protocol-based guidance is available for the management of specific adverse events (e.g., bradycardia with hemodynamic compromise). The primary responsibility for management of adverse events lies with the treating clinician.

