### Study Outline

This is a prospective dose-finding study of esmolol aiming to attenuate the sympathetic surge associated with severe TBI in adults. The setting is the 48-bed mixed ICU of Southmead Hospital, Bristol, a 996-bed teaching hospital in the southwest of England, and a major trauma center serving an adult population of approximately 2.3 million. On average, the ICU admits more than 130 patients with severe TBI annually.

The primary objective is to define a treatment dosage escalation schedule for esmolol for use in adults early (< 24 h) after severe TBI that balances the potential benefit of early exposure to beta-blockade with the ability to maintain adequate CPP. A reduction of heart rate of at least 15% from preinfusion baseline will be used as an indicator of clinically significant beta-blockade.

A group sequential adaptive model-based design (the CRM) will be used to determine the maximum tolerated dosage schedule for esmolol, defined as the highest dosing regimen associated with an acceptable level of toxicity. For the purpose of this study, this is taken to be a probability of dose-limiting toxicity of 10%. Dose-limiting toxicity is defined as failure to maintain CPP above the minimum recommended by Brain Trauma Foundation guidelines (60 mm Hg), despite standard interventions including vasopressors and the protocolized deescalation of the esmolol infusion such that withdrawal of esmolol is required, or the occurrence of a serious adverse event mandating withdrawal of the esmolol infusion.

Secondary objectives are to identify the effects of esmolol on organ function and to record clinical outcomes including mortality and function at 6 months. Exploratory objectives are to monitor the effects on biomarkers of sympathetic nervous system activity and to gather data to inform the design of a randomized controlled trial to establish feasibility and efficacy.

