### Study Intervention

Open-label esmolol is given as a continuous intravenous infusion at a dosage of 2.5–200 mcg.kg.min^−1^ titrated using a predefined dosage escalation schedule to achieve a heart rate reduction of ≥ 15% from baseline with CPP maintained above 60 mm Hg. The target heart rate will be set as the rolling mean over the preceding 5 min to avoid overshoots. Baseline is defined as the mean heart rate in the 4 h preceding confirmation of eligibility. The minimum permitted target heart rate will be 60 beats per minute, even if this is less than 15% reduction from baseline; the maximum will be 100 beats per minute, even if this is more than a 15% reduction from baseline. Actual body weight at the time of enrollment in the study (estimated or known) will be used for dosage calculations.

A starting dosage is defined for each cohort, with dosage increments for that cohort being 50% of the starting dosage. The dosage is reviewed and adjusted every 30 min as required to achieve the target heart rate (± 5 beats per minute). Titration to achieve heart rate control for short lived stimulating procedures (e.g., tracheal suction, positioning, portable chest X-ray) is not required. The infusion should be continued during procedures including surgery or within hospital transfers for imaging.

When the infusion is restarted after temporary suspension (e.g., for bradycardia or if heart rate maintained in target range without need for infusion), the starting dosage for that level will be used with increments every 30 min as required. The infusion should not be restarted after a temporary suspension until the heart rate exceeds the minimum target rate (or 60 beats per minute) for more than 15 min.

Esmolol infusion continues according to study protocol until one of the following stopping rules is met:Ninety-six hours from start of infusionHeart rate target achieved without esmolol for > 12 hDose-limiting toxicityDeath or withdrawal of life-sustaining treatmentRequest of participant, legal representative, or treating clinicianICU discharge or transfer to nonparticipating ICU

The esmolol is weaned in steps of 5–10 mcg.kg.min^−1^ every hour from 96 h to avoid rebound tachycardia. In the event of dose-limiting toxicity, it may be reduced more quickly or stopped immediately. In the event of ICU discharge or transfer to a nonparticipating ICU, the infusion will be reduced at a rate calculated to ensure at least 2 h without esmolol infusion prior to discharge.

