Bradycardia is defined for the purposes of this study as a heart rate under 50 beats per minute. The dosage of esmolol should be reduced in the appropriate increments for dosage level every 30 min until the bradycardia resolves.

Bradycardia with hemodynamic compromise is a heart rate under 50 beats per minute and a systolic blood pressure under 110 mm Hg (or 100 mm Hg for those aged 50–69 years). The dosage of esmolol should be reduced by twice the appropriate increment for dosage level every 30 min until bradycardia with hemodynamic compromise resolves.

When bradycardia is severe (defined as heart rate under 30 beats per minute), the esmolol infusion may be stopped temporarily until bradycardia resolves. Further intervention is at the discretion of the clinical team including intravenous antimuscarinic or chronotropic drugs and external or transvenous pacing.

Second-degree heart block without bradycardia or hemodynamic compromise should be managed by weaning esmolol as at the end of the intervention period. If hemodynamic compromise occurs, or in the event of third-degree heart block, management is the same as for severe bradycardia.

Hypotension should be managed according to usual clinical practice, taking into account cardiac status and CPP target. Fluid resuscitation and use of vasoactive agents including catecholamine and noncatecholamine vasopressors and inodilators are permitted. Esmolol infusion should be reduced in increments if these measures are insufficient to maintain CPP.

Flow charts for the management of esmolol infusion are shown in Figs. 2 and 3.

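### Non-serious bradycardia and heart block that settle when esmolol is reduced or weaned appear to fall outside the safety incidence, and their recording rests on a causality judgement: a cheap improvement to descriptive safety data

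*Protocol article*

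**What the plan says.** The Exploratory Outcomes section of the protocol article lists three hemodynamic safety outcomes, all ending in the same qualifier:

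- "bradycardia (heart rate < 50 beats per minute) with or without hemodynamic compromise requiring intervention other than reduction of esmolol" dosage;
- "second-degree or third-degree heart block with or without hemodynamic compromise requiring intervention other than reduction of esmolol" dosage;
- clinically significant hypotension, with age-dependent systolic limits: "< 110 mm Hg for others) requiring intervention other than reduction of esmolol" dosage.

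The Statistical Analysis section turns these into events per calendar day of infusion, a day counting if it has at least 12 h of infusion. They are reported overall and by category. Dose level is not mentioned.

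The Study Intervention section sets the response to the same events. For bradycardia: "The dosage of esmolol should be reduced in the appropriate increments for dosage level every 30 min until the bradycardia resolves". With hemodynamic compromise, the cut is twice the increment. "Second-degree heart block without bradycardia or hemodynamic compromise should be managed by weaning esmolol as at the end of the intervention period". The section also foresees suspension: "When the infusion is restarted after temporary suspension (e.g., for bradycardia" is one of its examples.

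Under Pharmacovigilance, all serious events are recorded. Other adverse events judged consistent with the patient's "critical illness do not require recording or reporting, unless the investigator considers they may relate to participation in the trial".

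Under Study Outline, a dose-limiting toxicity is either failure to maintain cerebral perfusion pressure such that esmolol must be withdrawn, or "the occurrence of a serious adverse event mandating withdrawal of the esmolol infusion".

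**The concern.** The response that the protocol prescribes for bradycardia is the response that keeps an episode out of the safety count. When the titration rules work as intended, the episode disappears from the reported incidence. Whether it is then captured as an adverse event depends on a judgement of cause in an open-label study without a control group, where bradycardia can plausibly be put down to the brain injury.

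The study's product is a dosage escalation schedule to be carried into later trials. How often a schedule had to be cut back for bradycardia or conduction block is part of its tolerability. Increments rise from 2.5 to 31 mcg/kg/min across the seven levels of Table 2, so the answer could differ by level. The stated outcomes would not show it.

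**Working it through.** The main check is a reading of the rules side by side. Take a non-serious fall in heart rate below 50, or a non-serious second-degree block, that resolves when esmolol is reduced or weaned.

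1. **Dose-limiting toxicity (Study Outline): no.** Cerebral perfusion pressure has not failed, and there is no serious adverse event mandating withdrawal.
2. **Bradycardia and heart block outcomes (Exploratory Outcomes): no, on the parallel reading.** The qualifier about needing other intervention could grammatically attach to the event or only to the hemodynamic compromise. The hypotension line has the same qualifier with no preceding clause about compromise, so there it can only describe the event. Reading the three lines alike, it describes the event in all three.
3. **Safety incidence (Statistical Analysis): no.** It counts the same outcomes and does not widen them.
4. **Mandatory serious-event recording (Pharmacovigilance): no**, by construction.
5. **Other adverse-event recording (Pharmacovigilance): conditional.** The episode is recorded if it is not attributed to critical illness, or if it is thought possibly related to the trial.
6. **Heart rate as a biomarker (Exploratory Outcomes): partial.** Heart rate is collected, and the general rule for continuous exploratory variables includes the minimum. A minimum shows that a low value occurred, but not how many episodes there were. The day-by-day biomarker list covers blood markers only. Heart block is not visible in a heart rate summary.

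Uncomplicated second-degree block is the clearest case. By its definition in Study Intervention it has neither bradycardia nor compromise, so neither the bradycardia nor the hypotension outcome picks it up, and the heart rate summary does not reveal it.

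**Scale of one omitted episode.** The protocol gives no expected frequency, and none is assumed here. Inputs: up to 96 h of infusion (Study Intervention); 24 patients, cohorts of three, and no escalation until the second cohort has completed the intervention (Statistical Analysis).

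- Qualifying days per patient: with a start at clock hour t, day 1 has 24 − t hours, days 2 to 4 have 24 hours each, and day 5 has t hours before weaning. Day 1 qualifies if t ≤ 12 and day 5 if t ≥ 12, so the total is 4 days, or 5 only for a start exactly at noon.
- All patients at full duration: 24 × 4 = 96 days; 1/96 = 0.010 events per day.
- A level with two cohorts: 6 × 4 = 24 days; 1/24 = 0.042.
- A level with one cohort: 3 × 4 = 12 days; 1/12 = 0.083.

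Earlier stopping would shorten the denominators and raise these values. They show what one episode weighs on the protocol's own measure; they are not evidence that any episode is lost.

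**Feasibility of capture.** Dosage is reviewed every 30 min: 96 / 0.5 = up to 192 reviews per patient, so a cut is seen when it is made.

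**The case against.** The other side has real points.

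- **The wording can be parsed differently.** If the qualifier belongs only to the compromise, all bradycardia and all block count, and reporting by category could be the split. Hypotension is itself a form of compromise, so its line had no need of a clause about compromise, which weakens the parallel. The narrower reading remains the more natural one, but it is a reading and not a certainty.
- **The recording waiver has the right exception.** The drug is a beta-blocker, the protocol tells staff to cut it for these events, and the event resolves when they do. Most such episodes would probably be judged possibly related. The Pharmacovigilance section itself gives bradycardia with compromise as an example of a specific adverse event. This largely stands; what remains is that capture is discretionary and produces no planned count by dose level.
- **Weaning and suspension may not be mere reduction.** The protocol does not say whether weaning to zero, or a temporary stop for severe bradycardia or third-degree block, counts as reducing the dosage. If it does not, some of these episodes are already included. That uncertainty is itself a reason to define the outcome.
- **Counting only what titration cannot handle is a defensible threshold** for a drug chosen for rapid offset. True, but the tolerability of a titration schedule includes how often it had to be reversed.
- **Table S1, the case report form and the full protocol are not shown.** They may collect these events. The point is therefore limited to the rules that the article states.

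A reader might infer that these events go unrecorded altogether, or that bradycardia would be invisible. The text supports neither: serious events are always recorded, possibly related ones are recorded, and heart rate is summarised.

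**Conclusion.** The point holds as a modest gap in descriptive safety reporting. On the more natural reading, non-serious bradycardia and heart block that resolve with esmolol reduction or weaning are not in the safety incidence, and their recording as adverse events depends on judged cause. The gap is clearest for non-serious second-degree block.

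The number of episodes affected is unknown. The conclusion rests on reading the qualifier alike in all three safety lines and on treating weaning as reduction.

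It would be tempting to conclude that toxicity is being hidden from the dose-finding model, or that the selected schedule would be biased. The documents do not support that. Dose-limiting toxicity is defined separately, deliberately around cerebral perfusion pressure and serious events, and these episodes are outside it whatever the safety outcomes count. The primary endpoint and the continual reassessment model are unaffected. The change is worth making because it is cheap and bears directly on the schedule being selected.

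**What to change.** Make three linked changes:

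1. In Exploratory Outcomes, define the bradycardia (below 50 beats per minute) and second- or third-degree heart block outcomes to include every episode, during infusion or weaning, that led to esmolol being reduced, suspended or stopped. This also settles whether suspension counts.
2. In Pharmacovigilance, add one sentence exempting these named events from the recording waiver. Record them whatever the judged cause, with attribution as a separate field.
3. In Statistical Analysis, add one descriptive table by dose level, split into episodes managed by esmolol change alone and episodes needing other intervention.

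The cost is modest extra recording by existing staff for 24 patients whose dosage is already reviewed every 30 min. The downside is that some recorded events will be due to the injury itself; the attribution field lets the reader see which were judged so.

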### Statistical Analysis

Inability to maintain CPP in the presence of esmolol was chosen as the primary definition of toxicity based on the known importance of adequate blood pressure for prevention of secondary brain injury [19]. The maintenance of adequate CPP as a key goal of therapy is also familiar to clinicians practicing in the field of neurointensive care.

Only data from esmolol-treated patients will be used in statistical analysis. Esmolol-treated patients are those who meet all inclusion criteria and no exclusion criteria, receive any dosage of esmolol within 2 h of confirmation of eligibility and 24 h of injury, and do not withdraw consent for use of data prior to use of that data in CRM analysis.

A one-parameter logistic model, initialized with skeleton parameters as per Table 2, will be used for the CRM modeling, with estimated probabilities revised as data emerge. This likelihood modeling algorithm will identify a maximum tolerated dose escalation schedule, with a defined prior reasoned target toxicity level, or “acceptable” toxicity rate (*θ*), of 10% with an indifference level of 2 percentage points for decision making. The weighting afforded to the pretrial logistic model on estimated probabilities will be revised as trial data sequentially emerge.

**Table 2 Tab2:** Predefined dose levels for esmolol infusion

Dose level	Starting dosage (mcg.kg.min^−1^)	Increment (mcg.kg.min^−1^)	Estimated prior probability of dose-limiting toxicity
1	5	2.5	0.01
2	10	5	0.04
3	16	8	0.07
4	25	12.5	0.10
5	35	17.5	0.15
6	46	23	0.20
7	62	31	0.25

Cohort size of three will be used. In the absence of dose-limiting toxicity, an increase in the dosage escalation schedule will be considered by the trial management group after the last patient in a cohort has completed the esmolol intervention period. Dosage escalation cannot be by more than one level and, as an additional safety measure, the dosage will not be escalated until the second cohort has completed intervention. Dosage deescalation will be considered after each dose-limiting toxicity and is unrestricted. Dosage level changes are subject to sponsor approval with oversight of dosage decision making the responsibility of the Steering Committee comprising independent expert and lay members. The Steering Committee is also responsible for monitoring study conduct and safety in lieu of formal Data Monitoring and Ethics Committee given the setting and design of the study.

The planned sample size of 24 esmolol-treated patients was determined in a pragmatic manner based on estimated recruitment rates following a test screening period in the ICU that were compatible with the timeline required by the funder and on the expected small information gain for additional patients over and above the target. This allows testing of up to seven dosage levels (Table 2).

In analysis of secondary and exploratory outcomes continuous variables will be summarized by descriptive statistics (mean and standard deviation, minimum, median, maximum, and interquartile range) and categorical data will be summarized in terms of frequency and percentage.

The Sequential Organ Failure Assessment will be reported as both daily total and by variable, excluding neurological assessment. Mortality outcomes will be analyzed using Kaplan–Meier survivorship. Length of stay and duration of mechanical ventilation will be analyzed using time to event Kaplan–Meier analyses. Both the number of patients with a bloodstream infection and the total number of bloodstream infections in ICU will be reported. The eGOS will be reported by category and dichotomized into favorable (eGOS 4–8) and unfavorable (eGOS 1–3) outcome, differentiating between patients who are independent at home or who are not. Quality of life (EQ-5D-5L) will be reported as the EQ-5D index and by each dimension.

Blood biomarkers (troponin, glucose, lactate, and International Normalized Ratio) will be reported for each day of the esmolol infusion. The incidence of safety outcomes is the number of events per calendar day of esmolol infusion (i.e., with at least 12 h of infusion) and will be reported as an overall incidence and by category. The dosage of vasopressor will be reported as noradrenaline equivalents in micrograms per kilogram per minute, with a correction factor of 10 used to convert from metaraminol.

The rate of recruitment reported as percent of screened population enrolled and as % of eligible population enrolled by month. Noncompliance with protocol, defined according to Sponsor’s Standard Operating Procedure as any breach of Good Clinical Practice or protocol, will be presented as total number of events and number of patients with episodes of noncompliance.

No subgroup or adjusted analyses are planned. There will be no imputation for missing data, which will be recorded as missing if queries are unable to recover the data. Some types of missing data represent study outcomes and will be reported as such.

Further quantitative analysis of relationships between outcomes or other study data will be undertaken with appropriate statistical methods. Qualitative analysis of acceptability will be undertaken using constant comparison methodology adapted from grounded theory with further details available via the Open Science Framework registration (https://osf.io/9ht4v). After publication, the data will be made available to other researchers on request if approved by the Trial Management Group and Sponsor.

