### Eligibility

Participants must meet all inclusion criteria and none of the exclusion criteria (shown in Table 1) and start the esmolol infusion within 2 h of confirmation of eligibility. The baseline heart rate must be > 60 beats per minute for more than 15 min for the infusion to start.

**Table 1 Tab1:** Eligibility criteria

Inclusion criteria (all to be met)	Exclusion criteria (none to be met)
1. Aged 18 years or more	1. Life or limb threatening extracranial injury (in the opinion of the treating intensivist)
2. Severe traumatic brain injury (Glasgow Coma Score of 8 or less after resuscitation or prior to intubation)	2. Perceived devastating brain injury admitted for the purposes of prognostication or organ donation
3. Within 24 h of injury	3. Participation in another clinical trial of investigational medicinal product within preceding 30 days
4. Intracranial pressure monitoring in situ	4. Pregnancy
	5. Breast feeding
	6. Hypersensitivity to beta-blockers
	7. Cardiogenic shock
	8. Decompensated heart failure (NYHA class 4)
	9. Untreated sick sinus syndrome or AV nodal conduction disorders including second-degree or third-degree heart block)
	10. Untreated phaeochromocytoma
	11. Acute severe bronchospasm
	12. Severe pulmonary hypertension (mean PA pressure > 55 mm Hg)
	13. Prinzmetal’s angina
	14. Severe metabolic acidosis (pH < 7.1)
	15. Use of verapamil within the preceding 48 h

AV, atrioventricular, PA, pulmonary artery, NYHA, New York Heart Association

These criteria exclude those at greatest risk of harm from beta-blockade, target early enrollment for greatest potential benefit and remain broad to capture a representative patient population.

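### The only analysis set is narrower than exposure to esmolol, so a toxicity in some dosed patients would be left out of the CRM and the safety tables

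*Protocol article*

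**What the plan says.** All points are from the protocol article.

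- **Statistical Analysis, population.** "Only data from esmolol-treated patients will be used in statistical analysis". No other population is described.
- **Statistical Analysis, definition.** "Esmolol-treated patients are those who meet all inclusion criteria and no exclusion criteria". On timing, the same definition requires that they "receive any dosage of esmolol within 2 h of confirmation of eligibility and 24 h of injury". The last condition concerns consent: a patient whose data were withdrawn before the CRM had used them is outside the set.
- **Eligibility.** Table 1 lists "3. Within 24 h of injury" as an inclusion criterion. The text adds that participants must "start the esmolol infusion within 2 h of confirmation of eligibility". Nothing in that section ties the infusion start itself to 24 h from injury.
- **Study Outline.** The primary objective concerns use of esmolol less than 24 h after injury.
- **Consent.** Data already used to calculate a dose are kept even if consent is later withdrawn.
- **Statistical Analysis, feasibility.** Recruitment is a percentage of the screened and of the eligible populations. Noncompliance covers any departure from the protocol or from Good Clinical Practice and "will be presented as total number of events and number of patients with episodes of noncompliance".

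**The concern.** The primary endpoint is a maximum tolerated schedule derived by the CRM. A dose-finding model should learn from toxicity in everyone exposed at a level. Here three kinds of exposed patient fall outside the only set: those who start esmolol more than 24 h after injury, those who start more than 2 h after eligibility is confirmed, and those later found ineligible. If one of them has a dose-limiting toxicity (DLT), the model and the safety incidence tables do not see it, and the estimate of toxicity at that level is too low.

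The first group also exposes a mismatch between sections. If the 24 h criterion is judged when eligibility is confirmed, a patient can comply with the Eligibility section and still be excluded.

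Read literally, the same sentence would also take out of the consent and noncompliance figures some of the withdrawals and breaches that those figures exist to count.

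**Working it through.** **1. The plan's own figure.** 24 patients in cohorts of 3 make 24/3 = 8 cohorts. Two cohorts must complete before the first escalation, so 2 are at level 1 and the other 6 can each move up one level: 1 + 6 = 7 levels. This agrees with the article. The 24 counts members of the analysis set, which suggests that an excluded patient would be replaced. Both cases are shown in step 3.

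**2. The time windows.** If inclusion is judged at confirmation, the latest confirmation is 24 h after injury and the latest permitted start is 24 + 2 = 26 h. The analysis set stops at 24 h. For scale only, assume that confirmation is uniform over 0 to 24 h and the lag L to infusion is uniform over 0 to 2 h. Then P(start after 24 h) = E[L]/24 = 1/24, or about 4%, which is about 1 patient in 24. The article gives no distribution for either time, and it aims for dosing as soon as practicable, so the true share may be lower.

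**3. What one omitted DLT does to the model.**

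Inputs from the article: Table 2 prior probabilities s = 0.01, 0.04, 0.07, 0.10, 0.15, 0.20, 0.25; target 10%; indifference level 2 points; one-parameter logistic model; escalation by at most one level.

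Assumed, because the article does not give them: logistic intercept 3; parameter b normal with mean 0 and variance 1.34 or 0.25; estimates taken at the posterior mean of b. A power model serves as a check.

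- Logistic: logit p_k = 3 + exp(b) × (logit s_k − 3)
- Power: p_k = s_k^exp(b)

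Data: 0/6, 0/3 and 0/3 at levels 1 to 3, then three patients at level 4, one of whom has a DLT. Estimated toxicity at level 4:

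| Model, prior variance | Counted (1/3) | Dropped (0/2) | Dropped and replaced (0/3) |
|---|---|---|---|
| Logistic, 1.34 | 10.9% | 0.0% | 0.0% |
| Logistic, 0.25 | 11.0% | 1.2% | 1.0% |
| Power, 1.34 | 11.4% | 0.5% | 0.4% |
| Power, 0.25 | 11.0% | 4.5% | 4.2% |

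When the DLT is counted, level 4 is closest to 10% in all four cases and the model stays. When it is dropped, the model points to level 7 (level 6 in the last row), so the one-level cap would allow level 5. With the patient dropped and not replaced, the estimate moves by about 6.5 to 11 points, against an indifference level of 2.

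**4. When one DLT is already counted.** On the same path with 15 patients and one counted DLT at level 4, adding an excluded patient with a DLT at that level raises the estimate from 10.9–11.4% to 18.5–19.7%. The recommendation falls from level 4 to level 2 (logistic with both variances, power with 1.34).

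**5. How likely it is.** If m dosed patients are excluded and each has the 10% target rate, P(at least one DLT among them) = 1 − 0.9^m. This gives 0.10, 0.19 and 0.27 for m = 1, 2 and 3.

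**The case against.** The strongest reply is that the plan does not ignore these patients. A DLT is defined by clinical events, without reference to the analysis set. All serious adverse events are recorded. De-escalation is to be considered after every DLT, and escalation is contemplated only when there has been none; neither rule is limited to the set. The Steering Committee oversees dosing and safety. A reader might infer that toxicity in an excluded patient goes unseen, or that the trial would automatically escalate. The documents do not support either inference. What stands is narrower: none of these safeguards enters the event into the model or the incidence tables, so a DLT could prompt a dose review and still be missing from the estimate that defines the primary endpoint.

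Three other strong readings also fail.

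- *Every feasibility rate is biased.* Recruitment has its own screened and eligible denominators, and the noncompliance definition covers late or ineligible dosing. The blanket sentence conflicts with these definitions; it does not clearly override them. Only consent after waiver and noncompliance need a clarifying statement.
- *All refusals are removed.* Only withdrawals made before the data reach the CRM are removed. Later ones stay in, and excluding the early ones may be legitimate.
- *Patients dosed at 24 to 26 h are plainly compliant.* That depends on when the 24 h criterion is judged. The objective's wording suggests that the limit may have been meant to apply to dosing.

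It can also be argued that restricting the CRM to eligible patients treated as specified is a defensible choice, and that an all-exposed safety listing may sit in a fuller document. The first argument supports a sensitivity analysis more than the only analysis. The second is weakened because the article says that this set alone is used.

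**Conclusion.** The point holds in limited form. As written, the analysis set leaves out patients who received esmolol late by either time limit or were later found ineligible, and a DLT in one of them would bias the maximum tolerated schedule upward. In the level 4 example, one such DLT separates an estimate of about 11% (stay) from one of 0 to 4.5% (escalation allowed by the model).

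The size is illustrative. It rests on an assumed intercept, prior variance and plug-in estimate, although the direction was the same in all four settings. It also takes for granted that an excluded patient has a DLT. With a single excluded patient at the target rate, the chance of that is 10%.

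The 24 to 26 h gap exists on one reading of the Eligibility section. On either reading, the Study Outline, Eligibility and Statistical Analysis sections do not state the same window and must be reconciled.

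**What to change.** 1. Define the CRM and safety set as every patient who received any esmolol, except those who withdrew consent for use of data before that data entered the CRM. Keep the existing rule that data already used for dosing are retained; a set that dropped every refuser would remove them.
2. Remove the eligibility and timing conditions from the set definition. Flag late-dosed and ineligible patients, and run one sensitivity CRM without them.
3. Reconcile the time window in Study Outline, Eligibility and Statistical Analysis, and say at which moment the 24 h criterion is judged. Which window applies is for the investigators to settle.
4. State that the sentence limiting analysis to esmolol-treated patients does not govern feasibility outcomes. Compute consent after waiver and noncompliance on all enrolled patients. Recruitment, as already defined, needs no change.

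The cost is wording and one extra model run, with no additional patients or data. The downside is that the primary set may contain a few patients outside the intended window or criteria, which the sensitivity run addresses.
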